**Figure 2 hsr22109-fig-0002:**
[figure not shown]
The main functionalities offered by the system. IBD, inflammatory bowel disease.

**Figure 3 hsr22109-fig-0003:**
[figure not shown]
Sign‐up of the “MY IBD BUDDY.”

**Figure 4 hsr22109-fig-0004:**
[figure not shown]
Home page of the “MY IBD BUDDY.”

In this application, there are various challenges and tasks for users to earn points. These points are awarded based on the user's progress displayed through the leaderboard and points table, level‐up, and progress bar to serve as an incentive for other users and to create competition. However, this competition is not related to caregiving tasks or medical test results, but rather to the number of interactions the user has with the system and, in fact, to the user experience within the system. For example, each user earns points by studying a chapter of the tutorial, doing gamifying tests, leveling up, and unlocking the next tutorial chapters. Additionally, by completing monitoring forms related to disease symptoms, medication registration, medication alert, test registration, and participating in educational challenges, the user earns points.

#### Group B (standard care)

2.7.2

The individuals in the conventional care group will receive IBD treatment from their gastroenterologist. The standard of care is based on current evidence‐based professional guidelines, which include a comprehensive assessment, a guideline‐concordant therapy plan, scheduled and as‐needed clinic visits, scheduled and as‐needed telephone calls, and the administration of educational fact sheets about disease‐specific topics as appropriate. They will be instructed to complete questionnaires online or by hand and will receive three complimentary visits to maintain their participation in the study. Participants in Group B will be given access to the gamified mobile‐based tele‐management program after 6 months of data collection.

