### Study procedure and design

2.4

In the present study, a gamified mobile‐based tele‐management system for patients with all types of IBD will be developed. To compare the impact of the gamified mobile‐based tele‐management system on health outcomes and outpatient visits in patients with all types of IBD, the authors will design a multicenter, parallel, two‐arm, exploratory randomized controlled trial with a 6‐month follow‐up per patient. IBD patients will be recruited from general practices and outpatient clinics after completing baseline questionnaires and providing informed consent. Subsequently, eligible patients will be randomly assigned to either (A) self‐management support through the use of the gamified mobile‐based tele‐management system (intervention group, MyIBD Buddy app), or (B) standard IBD care (control group). All patients will attend study visits at baseline, 12 and 24 weeks, and routine IBD clinic visits or telephone consultations based on randomization group assignment. Disease activity, anxiety and depression symptoms, quality of life, self‐efficacy, and IBD‐specific knowledge will be measured at baseline and during the 24‐week follow‐up. The Harvey–Bradshaw index (HBI) will measure disease activity among CD patients. Also, the disease activity among UC patients will be investigated using the simple clinical colitis activity index (SCCAI, also known as the Walmsley index). Notably, the Research Ethics Committee of Mashhad Faculty of Medical Sciences approved the current study in November 2021 (IR.MUMS.REC.1400.230). The trial prospectively registered is at IRCT (IRCT20200613047757N1) and visible at OSF (https://doi.org/10.17605/OSF.IO/AWFY9).

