### Sample size

2.5

With a significance level of 5%, statistical power of 80%, a correlation coefficient of at least 0.3 between the scales, and three measurements of the results—once at baseline and twice after randomization—repeated measures analysis will be used to calculate the sample size. The results of relevant publications will be used as the foundation for the analysis of covariance (ANCOVA) for various indicators. The sample size was calculated using the Sampsi module and the minimum clinically important difference (MCID) effect technique in the Stata 2015 environment. Consequently and based on the enormous sample size available for the quality of life index and accounting for the likelihood of a 20% dropout for each of the three measurements of the outcome, the sample size for this research is 105 participants in each group and 210 participants will be recruited.

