### Random assignment

2.6

Patients will be randomly assigned to the intervention or control group using a stratified block randomization sequence generated by WINPEPI, with the individual as the randomization unit. All IBD patients from the participating centers will be invited to participate in this investigation. An independent administrator will generate the allocation sequence and prepare 210 numbered, opaque, sealed envelopes containing assignments distributed equally between the two study groups. Each participant will be notified via email or the social network of their designated group and given instructions on how to access the relevant app or online survey.

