#### Group A or intervention (gamified mobile‐based tele‐management system)

2.7.1

Participants in the gamified mobile‐based tele‐management system (MyIBD Buddy application) group will receive instructions on using the system and a username and password which will be valid for up to 6 months via standard care. The application was developed for the Android platform using the Suker Wheel game development framework. The research team closely collaborated with the development team and the five‐step ADDIE design model was utilized. The goal was to combine behavior modification strategies and self‐management theory. The educational content of this application has been studied and validated by the research team in our previous work.^16^, ^17^, ^18^, ^19^, ^36^ The study outlines the development process of an application aimed at teaching self‐care techniques, including self‐care skills and psychological aspects such as stress and anxiety control, to monitor patients' physical and mental status, including self‐care skills and psychological aspects such as stress and anxiety control, to monitor patients' physical and mental status, relaxation and mindfulness techniques.

The main functionalities of the MY IBD Buddy application include the following components (Figures 2, 3, 4):
Login page includes user information and disease registration.Patient disease profile (clinical disease history, body mass index calculator).Tele‐monitoring, including five components (tracking symptoms related to IBD):
1.Interaction monitoring (assessing satisfaction with the application).2.Psychological and mental health monitoring (monitoring anxiety and depression, IBD quality of life, and IBD self‐efficacy).3.Medical monitoring (disease activity using disease activity and providing feedback, fecal calprotectin levels monitoring).4.Educational monitoring (assessing knowledge related to the IBD).5.Nutritional monitoring (food diary).

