### Data collection and study outcomes

2.9

Table 1 shows the data extraction procedure.

**Table 1 hsr22109-tbl-0001:** The procedure of data collecting.

Measure	Measurement method
Primary outcomes	
Quality of life	HRQOL will be measured using the IBDQ^20^ The IBDQ contains 32 items divided into four health subdimensions: bowel symptoms, systemic symptoms, social functioning, and emotional function. The total score ranges from 32 to 224, and a higher score indicates a better quality of life.^20^, ^21^ A clinically significant change score is +16.^22^, ^23^, ^24^, ^25^
Disease activity scores	Disease activity scores are calculated using the HBI^26^ for participants with CD and the SCCAI^27^ for participants with UC/indeterminate colitis. Patients with CD and an HBI < 5 will be considered to be in clinical remission, whereas patients with scores of 5–7, 8–16, or >16 will be classed, respectively, as having mild, moderate, or severe activity.^26^ For patients with UC, clinical remission will be defined as an SCCAI ≤ 2, whereas values of 3–5 or >5 points will be classed as mild‐to‐moderate or severe activity.^28^
Anxiety and depression	Hospital Anxiety and Depression Scale (HADS): The 14 items on the HADS are equally divided between the HADS‐Anxiety and HADS‐Depression subscales. Subscale scores of 8–10 are categorized as borderline and 11–21 as clinical.^29^, ^30^ A clinically significant change score is −1.5 to −2 points.^31^, ^32^
Secondary outcomes	
Self‐efficacy	Self‐efficacy will be measured with the 29‐item inflammatory bowel disease self‐efficacy scale (IBD‐SES)^33^ Questions are grouped into four domains: managing stress and emotions, managing medical care, managing symptoms and disease, and maintaining remission. Overall scores on the IBD‐SES range from 29 to 290, with higher scores indicating higher self‐efficacy and thus better self‐management and greater patient empowerment.
Patient knowledge	As assessed by the IBD‐KNOW, patient knowledge will be compared between groups. The total score ranges from 1 to 24, and a higher score indicates a higher disease knowledge.^34^
Patient satisfaction (user experience)	Using a 5‐point figurative scale from 1 (*very satisfied*) to 5 (*not satisfied*).

*Note*: Follow‐ups will be done at 0, 12, and 24 weeks after randomization except for the last item.

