### Statistical analysis

2.11

These models' adjusted intervention effects and 95% confidence interval and *p* values will be provided. Statistical significance will be determined by a two‐sided *p* value > 0.05. Statistical analysis will be conducted to understand the characteristics of patients with missing data.

Using SPSS's multiple imputation approach, missing data at the case level will be imputed. For the statistical analysis, SPSS V.22 will be used.

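### The article sets a questionnaire route for controls only and implies the app for the intervention arm; one common route outside the app should be stated for both

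*Protocol article*

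**What the plan says.** **Control arm.** Section 2.7.2 of the protocol article: "They will be instructed to complete questionnaires online or by hand and will receive three complimentary visits to maintain their participation in the study".

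**Route by arm.** Section 2.6 says that each participant is told the assigned group and "given instructions on how to access the relevant app or online survey".

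**What the app measures.** The functions in section 2.7.1 include "monitoring anxiety and depression, IBD quality of life", self-efficacy, disease knowledge, and disease activity with feedback. Later in 2.7.1, on rewards: "by completing monitoring forms related to disease symptoms, medication registration, medication alert, test registration, and participating in educational challenges, the user earns points".

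**What is common to both arms.** Table 1 (section 2.9) lists one set of instruments. Its note says that follow-ups "will be done at 0, 12, and 24 weeks after randomization except for the last item". Section 2.4 has every patient attend study visits at baseline, week 12 and week 24, with baseline questionnaires completed before randomisation.

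**Visits.** Section 2.4 states the aim of comparing the system's impact "on health outcomes and outpatient visits in patients with all types of IBD".

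**Masking.** Section 2.8 leaves participants and the programme coordinator unblinded.

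**The concern.** The constructs that the app monitors are those of the primary outcomes (IBDQ, HADS, HBI/SCCAI) and of two secondary outcomes (IBD-SES, IBD-KNOW). No section separates the app's monitoring from trial measurement, and a route is stated for one arm only. On a natural reading of 2.6 and 2.7.2, Group A answers in the app and Group B answers by survey or on paper.

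If so, answers after baseline come from different settings. One is an app with points, a leaderboard and feedback on disease activity. The other is a plain form. Participants know their arm, and section 3.1 itself names self-report as a source of reporting bias. Its remedy, a high response rate, does nothing about a difference between arms. A shift caused by the setting would be reported as an effect of the app, or would hide one.

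A smaller issue concerns visits. Complimentary visits are described for controls only, yet outpatient visits are to be compared between arms.

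**Working it through.** **Step 1: passages side by side**

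| Item | Intervention arm | Control arm |
|---|---|---|
| Route for trial questionnaires | Not stated; app implied (2.6) | Online or on paper (2.7.2) |
| Same constructs monitored in the app | Yes (2.7.1) | No app access until data collection ends (2.7.2) |
| Feedback | Stated for disease activity (2.7.1) | None stated |
| Points for forms | Stated for symptom forms (2.7.1) | None |
| Study visits | Baseline, weeks 12 and 24 (2.4) | Same (2.4) |
| Complimentary visits | Not mentioned | Three (2.7.2) |

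**Step 2: can baseline adjustment help?** Section 2.4 places the baseline questionnaires before randomisation, so before app access. A change of route in one arm would start after baseline. It would then enter the change from baseline (2.11.1) and any baseline-adjusted difference in full.

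**Step 3: the plan's own sample size.** Section 2.5 gives 105 per arm. Its inputs are "With a significance level of 5%, statistical power of 80%, a correlation coefficient of at least 0.3 between the scales", three measurements and 20% dropout. It gives no SD, so 105 can be neither reproduced nor refuted. With 16 IBDQ points (the clinically significant change in Table 1) as the difference, 105 × 0.8 = 84 evaluable per arm, and the ANCOVA variance factor (1 + 0.3)/2 − 0.3² = 0.56, the implied SD is 16 × √(84/(2 × 0.56))/2.80 ≈ 49.5.

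**Step 4: illustration of a pure measurement shift.** The shift *b* is assumed, because the documents give none. Section 2.11 sets sidedness: "Statistical significance will be determined by a two‐sided" p value.

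A standard error giving 80% power for 16 points is 16/(1.96 + 0.8416) = 5.71. With no true effect, the rejection rate is Φ(b/5.71 − 1.96) + Φ(−b/5.71 − 1.96).

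| Assumed shift (IBDQ points) | False-positive rate |
|---|---|
| 0 | 5.0% |
| 2 | 6.4% |
| 4 | 10.8% |
| 6 | 18.3% |

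In SD units, with 84 evaluable per arm, SE = √(2 × 0.56/84) = 0.115. Shifts of 0.05, 0.10 and 0.20 SD give about 7%, 14% and 41%. With no variance reduction (factor 1) they give about 6%, 10% and 25%.

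The sign is equally unknown. A 4-point shift against the app, with a true 16-point effect, would cut power from 80% to Φ((16 − 4)/5.71 − 1.96) ≈ 56%.

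**The case against.** **The strongest defence** is that nothing in the article says that the week 12 and week 24 scores of Group A come from the app. Visits, instruments and times are common to both arms, the wording in 2.6 can be read as instructions for reaching the intervention, and 2.7.1 describes monitoring as an app function. This stands against any flat statement that outcomes are collected differently. It does not dispose of the point, because the article does state a route, for one arm only, and nothing excludes in-app scores.

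**Self-monitoring is part of the intervention.** This also stands. Its effect on patients is partly what the trial tests. The problem would be using the monitoring as the outcome measure. A common form makes the route equal, but it does not remove Group A's greater familiarity with the questions, nor should it.

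**Readings that go too far:**
- A reader might infer that feedback and points attach to the IBDQ and HADS. The text states feedback for disease activity and points for symptom forms. It also says that the competition concerns the number of interactions, not test results.
- A reader might see a contradiction between week 0 after randomisation in Table 1 and baseline before randomisation in 2.4. Week 0 is ordinary shorthand for baseline, and 2.4 already gives the right order.
- A reader might multiply 3 visits by 105 controls and conclude that the design adds 315 visits. The three complimentary visits may simply be the three study visits that everyone attends, in which case the excess is zero. Outpatient visits are also not among the outcomes in Table 1.

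**Conclusion.** The point holds as a conditional one. The article fixes a route for controls, implies the app for the intervention arm, and leaves open whether in-app scores are trial outcomes. If they are, every primary outcome is measured under different conditions by arm after baseline, in unblinded participants. No baseline adjustment can separate that from the app's effect.

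The size is unknown. The figures above rest on an assumed shift and, for the IBDQ-point version, on 16 points having been the design difference, which section 2.5 does not state. They show only that a modest shift would matter. They are not an estimate of bias in this trial.

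The status of the complimentary visits is a separate ambiguity that needs a sentence of clarification. The change should be made because it is cheap and because an arm-specific route could not be repaired in the analysis.

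**What to change.** 1. State that the IBDQ, HADS, HBI/SCCAI, IBD-SES and IBD-KNOW are collected in both arms on one identical form outside the app, at the baseline, week 12 and week 24 study visits that all patients already attend.
2. State that no in-app monitoring score is used as a trial outcome and that no points are given for trial questionnaires.
3. Say whether the three complimentary visits are the common study visits or extra visits for controls only. Exclude study and complimentary visits from the outpatient-visit comparison in both arms.

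The cost is low, since an online survey and the common visits already exist. The one downside is that app users will answer some questions twice around weeks 12 and 24.

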### Masking

2.8

Participants and the program coordinator cannot be blinded to participant study allocation due to the nature of the intervention. However, the statistician who will validate the data analysis will be blinded to the randomization groups.

### Data collection and study outcomes

2.9

Table 1 shows the data extraction procedure.

**Table 1 hsr22109-tbl-0001:** The procedure of data collecting.

Measure	Measurement method
Primary outcomes	
Quality of life	HRQOL will be measured using the IBDQ^20^ The IBDQ contains 32 items divided into four health subdimensions: bowel symptoms, systemic symptoms, social functioning, and emotional function. The total score ranges from 32 to 224, and a higher score indicates a better quality of life.^20^, ^21^ A clinically significant change score is +16.^22^, ^23^, ^24^, ^25^
Disease activity scores	Disease activity scores are calculated using the HBI^26^ for participants with CD and the SCCAI^27^ for participants with UC/indeterminate colitis. Patients with CD and an HBI < 5 will be considered to be in clinical remission, whereas patients with scores of 5–7, 8–16, or >16 will be classed, respectively, as having mild, moderate, or severe activity.^26^ For patients with UC, clinical remission will be defined as an SCCAI ≤ 2, whereas values of 3–5 or >5 points will be classed as mild‐to‐moderate or severe activity.^28^
Anxiety and depression	Hospital Anxiety and Depression Scale (HADS): The 14 items on the HADS are equally divided between the HADS‐Anxiety and HADS‐Depression subscales. Subscale scores of 8–10 are categorized as borderline and 11–21 as clinical.^29^, ^30^ A clinically significant change score is −1.5 to −2 points.^31^, ^32^
Secondary outcomes	
Self‐efficacy	Self‐efficacy will be measured with the 29‐item inflammatory bowel disease self‐efficacy scale (IBD‐SES)^33^ Questions are grouped into four domains: managing stress and emotions, managing medical care, managing symptoms and disease, and maintaining remission. Overall scores on the IBD‐SES range from 29 to 290, with higher scores indicating higher self‐efficacy and thus better self‐management and greater patient empowerment.
Patient knowledge	As assessed by the IBD‐KNOW, patient knowledge will be compared between groups. The total score ranges from 1 to 24, and a higher score indicates a higher disease knowledge.^34^
Patient satisfaction (user experience)	Using a 5‐point figurative scale from 1 (*very satisfied*) to 5 (*not satisfied*).

*Note*: Follow‐ups will be done at 0, 12, and 24 weeks after randomization except for the last item.

Abbreviations: CD, Crohn's disease; HRQOL, health‐related quality‐of‐life; IBDQ, inflammatory bowel diseases questionnaire; SCCAI, simple clinical colitis activity index; UC, ulcerative colitis.

### Data management

2.10

First, the characteristics of the patients in the test and control groups will be documented, and any differences between the groups will be assessed using tests to measure variations in means or proportions. Second, the intergroup variations in disease outcomes will be assessed using multivariable linear regression which will be adjusted for the following stratification criteria: subtypes of IBD (CD or UC), disease activity at baseline (remission or active), age (numerical), sex (male or female), disease duration (numerical), smoking (nonsmoker, active smoker, or ex‐smoker), and educational level (five levels). For missing outcomes and variables, the multiple imputation approach will be used to impute the missing data. Results will be adjusted for age, sex, and illness duration, disease activity at baseline, educational attainment, and stratification criteria.

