### Study setting

2.2

Adult IBD patients will be recruited in person from three Iranian adult gastroenterology and Hepatology centers. A local research coordinator will explain the study to eligible patients and obtained written consent.

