### Study groups

2.7

After obtaining informed consent, the patients will be stratified by disease type, disease activity, and location of outpatient appointments. The participants will then be assigned to the intervention (A) or control (B) group according to the procedure described in 2.7. The groups are described in the following sections.

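### The regression's list of stratification criteria does not match the factors used to stratify: outpatient location is absent, five prognostic covariates are mislabelled, and no continuous baseline outcome score is named

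*Protocol article*

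**What the plan says.** Section 2.6 (Random assignment) assigns patients "using a stratified block randomization sequence generated by WINPEPI, with the individual as the randomization unit". Section 2.7 (Study groups) names the factors: "the patients will be stratified by disease type, disease activity, and location of outpatient appointments".

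Section 2.10 (Data management) plans a multivariable linear regression of disease outcomes, "adjusted for the following stratification criteria: subtypes of IBD (CD or UC), disease activity at baseline (remission or active"; the list continues with "age (numerical), sex (male or female), disease duration (numerical), smoking (nonsmoker, active smoker, or ex‐smoker), and educational level (five levels". The same section closes: "Results will be adjusted for age, sex, and illness duration, disease activity at baseline, educational attainment, and stratification criteria". Section 2.11 says the adjusted effects from these models will be reported with confidence intervals and p values.

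Section 2.5 (Sample size) refers to ANCOVA, with one baseline and two later measurements: "With a significance level of 5%, statistical power of 80%, a correlation coefficient of at least 0.3 between the scales". Table 1 has IBDQ, HBI or SCCAI, and HADS measured at weeks 0, 12 and 24.

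Section 2.11.1 plans repeated measures ANOVA at these time points and on change from baseline, for disease activity within disease type. It names no baseline covariate.

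**The concern.** Three things in the adjustment plan do not fit together.

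- **A stratifier is lost.** Stratified blocks make the arms alike on outpatient location. A model without location does not credit that balance, so its standard error is too wide wherever location is related to outcome.
- **One term has two meanings.** Section 2.10 first defines stratification criteria by a seven-item list, then names five of those seven separately from stratification criteria. Which variables enter the adjusted model therefore depends on the reader, and the adjusted effects are the ones to be reported.
- **The baseline score is not a covariate.** For IBDQ and HADS no baseline value is listed. For disease activity only a remission/active flag appears. The sample size section refers to ANCOVA, whose gain comes from using the baseline score as a covariate.

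**Working it through.** **Step 1: the lists side by side**

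| Variable | Stratifier (2.7) | First list (2.10) | Named in closing sentence (2.10) |
|---|---|---|---|
| Disease type | yes | yes | no |
| Disease activity | yes | yes (two levels) | yes |
| Outpatient location | yes | no | no |
| Age | no | yes | yes |
| Sex | no | yes | yes |
| Disease duration | no | yes | yes |
| Smoking | no | yes | no |
| Education | no | yes | yes |
| Continuous baseline score of the outcome | no | no | no |

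There are three stratifiers and seven listed items. Two overlap, one stratifier is absent and five items are not stratifiers.

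The closing sentence also adds the stratification criteria as a group. If that term has the 2.7 meaning, location and disease type enter and smoking does not. If it has the meaning given by the first list, smoking and disease type enter and location does not. The two readings give different models.

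**Step 2: the plan's own sample size**

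The figure of 105 per arm cannot be reproduced, because section 2.5 states neither a standard deviation nor the difference used. Suppose the difference is the 16 IBDQ points in Table 1, the method is ANCOVA at r = 0.3, and 20% drop out, leaving 105 × 0.8 = 84 evaluable per arm. Then 84 = 2 × 7.849 × SD² × 0.56 / 16² gives SD ≈ 49.5. The ratios in Step 4 do not depend on this value.

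**Step 3: leaving out location**

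Assume that location is well balanced by the stratified blocks and explains a share R² of the variance left after disease type and disease activity. The documents give no R²; 5% to 10% is an assumption. The true variance of the treatment contrast is then (1 − R²) times what the model reports, so the two-sided error is 2 × [1 − Φ(1.96 / √(1 − R²))].

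- R² = 0.05: 1.96 / √0.95 = 2.011, error 4.4%; sample-size equivalent 1 / 0.95 = 1.05
- R² = 0.10: 1.96 / √0.90 = 2.066, error 3.9%; sample-size equivalent 1 / 0.90 = 1.11

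**Step 4: leaving out the baseline score (illustration)**

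Assumptions: the outcome is the mean of the two follow-ups, and one correlation r applies between all pairs of time points. The variance factors, relative to a single measurement, are:

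- baseline ignored: (1 + r) / 2
- change score: (1 + r) / 2 + 1 − 2r
- ANCOVA: (1 + r) / 2 − r²

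At r = 0.3 these are 0.65, 1.05 and 0.65 − 0.09 = 0.56.

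If ANCOVA has 80% power at two-sided 5%, the power of another method with factor F is Φ(2.802 × √(0.56 / F) − 1.96):

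- baseline ignored: 2.802 × √(0.56 / 0.65) = 2.600; Φ(0.640) = 74%
- change score: 2.802 × √(0.56 / 1.05) = 2.046; Φ(0.086) = 53%

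The protocol says at least 0.3. At r = 0.5 with the same sample, the factors are 0.50 for ANCOVA and 0.75 for each of the others: power 84% against 68%.

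**The case against.** Much can be said for the plan.

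- **Baseline is not ignored throughout.** A reader might infer that the repeated measures ANOVA adjusts for nothing. Section 2.11.1 does not support that: disease activity is analysed within disease type, baseline is one of the time points, and change from baseline is analysed. What stands is that no baseline covariate is stated, and a change score is not ANCOVA.
- **Smoking.** A reader might infer that the closing sentence drops smoking as well as location. No single reading drops both. What stands is the ambiguity.
- **The five extra covariates.** Adjusting for them is acceptable. The fault is the label, and the label matters because it takes the place of a real stratifier.
- **The power figures describe no stated analysis.** Section 2.10 does not say whether the regression outcome is a level or a change, one visit or an average. Section 2.5 does not say that its correlation applies between all visits. The remission/active flag and the other covariates may recover part of the loss for a level outcome. All of this stands, so the figures are illustrative.
- **Scope of the regression.** If disease outcomes in 2.10 means disease activity only, baseline IBDQ and HADS would not be expected there. Even then, baseline activity enters only in two levels.
- **Meaning of location.** Recruitment is described as "recruited in person from three Iranian adult gastroenterology and Hepatology centers", so location most naturally means centre, but section 2.4 also mentions general practices. The protocol's own term is the safer one.
- **Direction.** The location effect is conservative and rests on an assumed R².

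**Conclusion.** The point holds as a mismatch between the design and the adjustment plan. Section 2.10 leaves out one of three stratifiers, labels five prognostic covariates as stratifiers, uses one term in two senses, and names no continuous baseline outcome score despite the ANCOVA reference in section 2.5. The list comparison rests on the text alone.

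The size is modest. For location, it is a true error of 4.4% to 3.9% instead of 5%, if location explains 5% to 10% of residual variance. For the baseline score, the illustration gives about 74% (baseline wholly ignored) or about 53% (change scores) where ANCOVA would have 80%, under a common correlation of 0.3 and the mean of two follow-ups.

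A reader might infer that the trial's power is 74%, or that 105 per arm is wrong. Neither follows: the illustrated analyses are not ones the protocol states, and the sample size cannot be checked without a standard deviation. Nor is there any sign of bias or of too many false positives from this source.

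**What to change.** Replace both lists in section 2.10 with one covariate set for the outcome models:

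- disease type, baseline disease activity (remission or active) and outpatient location, identified as the three stratification factors;
- the continuous baseline score of the outcome analysed: IBDQ, the HADS subscale, or HBI or SCCAI within its disease type;
- age, sex, disease duration, smoking and education, identified as prognostic covariates and not as stratification criteria.

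State how location is coded, and say in section 2.11.1 whether the same set applies to the repeated measures models.

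The cost is wording only. Location is needed to randomise and the scores are taken at week 0, so no new data are required. If location means the three centres, it uses two degrees of freedom and the baseline score one, in a trial of 210 patients.

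### The adjusted regression codes baseline disease activity as remission or active although the HBI or SCCAI score is collected, which costs that model some precision for the disease-activity outcome

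*Protocol article*

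**What the plan says.** Section 2.10 (Data management) states that "the intergroup variations in disease outcomes will be assessed using multivariable linear regression". Its list of adjustment variables includes IBD subtype and "disease activity at baseline (remission or active), age (numerical"; disease duration is numerical too. The section calls the whole list stratification criteria, although section 2.7 stratifies only by disease type, disease activity and clinic location. The last sentence of section 2.10 gives a second adjustment list that includes "disease activity at baseline, educational attainment, and stratification criteria". There, baseline disease activity stands apart from the stratification criteria and has no stated form.

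Section 2.11 opens by promising adjusted effects with 95% confidence intervals and p values from these models.

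Table 1 (section 2.9) makes disease activity a primary outcome: "Disease activity scores are calculated using the HBI" in Crohn's disease, and with the SCCAI in ulcerative or indeterminate colitis. Measurements are at "0, 12, and 24 weeks after randomization except for the last item", so a numeric score exists at baseline. Above the remission cut-off, HBI scores of 5–7, 8–16 and over 16 "will be classed, respectively, as having mild, moderate, or severe activity". For the SCCAI, 3–5 and over 5 "points will be classed as mild‐to‐moderate or severe activity".

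Section 2.11.1 (Primary study analysis) compares mean disease activity at all visits, and change since baseline, by repeated measures ANOVA separately by disease type.

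**The concern.** For a numerical outcome, the baseline value of that outcome is usually the most informative covariate. In section 2.10 it is the one cut in two. A patient with an HBI of 5 and one with an HBI above 16 have the same baseline value in the regression.

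Two things are at stake in that model. The confidence interval is wider than the collected data allow. And if one arm happens to receive the more severe of the active patients, the regression cannot adjust for it. If the randomisation strata are remission and active, as section 2.10 suggests, stratification does not balance severity within the active class either.

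This is not a detail left to a fuller document: the article spells out the form of the covariate.

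**Working it through.** **The plan's own figure.** The protocol gives no precision figure for this outcome. Its sample size of 105 per group rests on quality of life. With one baseline and two follow-up measurements and r = 0.3, the ANCOVA factor is (1 + r)/2 − r² = 0.65 − 0.09 = 0.56. Taking the Table 1 change of 16 IBDQ points as the difference (an assumption) and 105 × 0.8 = 84 analysed per group, 84 = 2 × 0.56 × (2.8016 × SD/16)² gives an SD of about 49.5. No SD is stated, so 105 can be neither reproduced nor refuted, and it does not depend on this point.

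**Inputs.**
- Correlation r: section 2.5 gives at least 0.3, worded as between the scales. It is read here as baseline to follow-up, and is not stated to be for HBI or SCCAI. The values 0.5 and 0.7 are assumptions.
- Share in remission p: not stated; 50–70% assumed.
- Score roughly normal: assumed.
- Regression outcome: taken as the follow-up score; the protocol does not say.

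**Formulas.** A cut at proportion p keeps a share k = φ(z_p)²/[p(1 − p)] of r². This gives k = 0.637 at p = 0.5, 0.622 at 0.6 and 0.576 at 0.7. Residual variance is 1 − r² with the continuous score and 1 − k·r² with two levels. Power, where the score would give 80%, is Φ(2.8016/√ratio − 1.96). The equivalent loss per group is 105 × (1 − 1/ratio).

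| r | 1 − r² | 1 − k·r² | Variance ratio | Extra SE | Power | Equivalent loss of 105 |
|---|---|---|---|---|---|---|
| 0.3 | 0.910 | 0.943–0.948 | 1.036–1.042 | 1.8–2.1% | 78.6–78.4% | about 4 |
| 0.5 | 0.750 | 0.841–0.856 | 1.121–1.141 | 5.9–6.8% | 75.4–74.6% | 11–13 |
| 0.7 | 0.510 | 0.688–0.718 | 1.349–1.408 | 16.2–18.6% | 67.4–65.6% | 27–30 |

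For the mean of two follow-ups at r = 0.3 and a median split: (0.65 − 0.637 × 0.09)/(0.65 − 0.09) = 0.593/0.560 = 1.058, or 2.9% in SE and 77.7% power.

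**Check without normality.** A simulation used 84 per arm, a skewed (gamma) score, 50% in remission, assignment stratified on remission/active, and 4000 runs. The variance of the treatment effect, relative to adjusting for the score, was:

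| r | Two-level covariate | Unadjusted change score |
|---|---|---|
| 0.3 | 1.04 | 1.26 |
| 0.5 | 1.14 | 1.17 |
| 0.7 | 1.49 | 1.07 |

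Despite the stratification, the arm difference in baseline score among active patients had an SD of about 0.21 baseline SDs. The two-level regression leaves r times such a difference in the contrast among active patients: for one of 0.21, that is 0.06 at r = 0.3 and 0.15 at r = 0.7.

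**The case against.** The strongest reply is section 2.11.1. The analysis labelled primary there uses the numeric baseline, so a reader who infers that severity imbalance goes uncorrected throughout the trial goes too far. That stands, and it limits the point to the section 2.10 regression. It does not remove it. Subtracting the baseline over-corrects when r is below 1 and, in the simulation, was less precise than adjusting for the score at every correlation tried.

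Second, the last sentence of section 2.10 may mean that baseline activity is a covariate in its own right, next to a two-level stratification factor. That reading is possible. But the sentence gives no form, while the earlier one in the same section gives an explicit two-level coding, so the ambiguity needs settling.

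Third, remission/active has a rationale: it is defined for both diseases, and one raw score cannot serve HBI and SCCAI in a pooled model. This stands, and it shapes the fix.

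Fourth, the loss at r = 0.3 is small, and the larger figures rest on assumed correlations. Both statements are correct. The protocol's wording makes 0.3 a floor, but nothing in it establishes 0.5 or 0.7 for these scores.

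Fifth, if the regression outcome is change from baseline, imbalance is already subtracted and the variance ratios in the first table do not apply. The protocol does not say which outcome form is meant.

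**Conclusion.** The point holds for the adjusted regression in section 2.10, whose effects and intervals section 2.11 says will be reported. With the follow-up score as outcome, the two-level baseline costs about 4% in residual variance and about 2% in SE at r = 0.3. With a roughly normal score and 50–70% in remission, it costs 12–14% at r = 0.5 and 35–41% at r = 0.7. It also leaves chance severity imbalance among active patients unadjusted in that model.

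A reader might infer systematic bias. The documents do not support that: under stratified randomisation the remaining imbalance is due to chance, the confidence interval reflects it on average, and the cost is precision. Nor do they support a claim that the sample size is wrong on this account, or that the loss is large: at the protocol's only stated correlation it is small. The case for change is that the gain is nearly free.

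**What to change.** In section 2.10, state that for the disease-activity outcome the regression includes the continuous baseline score: HBI in Crohn's disease, SCCAI in ulcerative or indeterminate colitis. Fit it separately by disease type, as section 2.11.1 already does, or in one model with a disease-type-by-score interaction, because the scales differ. Keep remission/active as the stratification factor. Give the same form for baseline disease activity in the section's last sentence.

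Once the baseline score is a linear covariate, the treatment effect is the same whether the outcome is written as the follow-up score or as change, so that ambiguity no longer matters to the result.

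The cost is a line or two of text and one or two more model terms, or separate models by disease type. No new data are needed, as the score is already collected at week 0.
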